## Abstract

**Background:**

Appropriate antibiotic prescribing for routine childhood illnesses in ambulatory settings remains a major challenge especially at scale. The frequent overuse and misuse of antibiotics may lead to side effects in the children receiving them and contribute to the emergence of antibiotic-resistant bacteria. Substantial evidence suggests that adherence to established antibiotic prescribing guidelines curtails negative consequences without compromising treatment outcomes. However, adoption of guidelines remains stubbornly static. Implementation studies show specific strategies are effective at improving antibiotic stewardship (e.g., audit and feedback, electronic medical records [EMR] tools); however, there is limited evidence on how these strategies function when implemented across a large health system. As a large integrated health system, Intermountain Health (IH) is well-positioned for a scaled implementation of guideline-concordance antibiotic stewardship for acute respiratory tract infections (ARTIs) in children due to its previous stewardship work, culture of continuous quality improvement, and implementation infrastructure.

**Methods:**

This study will evaluate the implementation of guideline-concordance prescribing for Acute Respiratory Tract Infections (ARTIs) in children 6 months to less than 18 years of age in ~ 250 sites across 5 care specialties (pediatrics, family medicine, urgent care, emergency department, and telehealth). The evaluation will focus on: (1) the overall effectiveness of implementation strategies at driving adherence to guideline-concordant care across the organization, (2) the nature of variability in strategy implementation and adherence by context (e.g., specialty, rurality, region), and (3) the utility of a more intensive implementation, termed “Boost,” for sites with lower adherence after general implementation. Primary effectiveness outcome is adherence to guideline-concordant antibiotic *selection.* Secondary outcomes include adherence to guideline-concordant antibiotic prescription *duration*, and the combination of *both selection and duration* termed Recommended Antibiotic and Duration Adherence Rate (RADAR). We will employ an observational, quasi-experimental approach comparing adherence before and after implementation in two waves across the organization and pre-post Boost for sites selected for intensive implementation support. In addition, we will investigate the correlations between use of implementation strategies and changes in adherence.

**Discussion:**

This study aims to fill a critical gap in the literature concerning implementation of antibiotic stewardship at large scale. Following established implementation science regarding effective implementation strategies, this evaluation tests their utility across diverse settings thus enabling investigation of contextual determinants. In addition, the evaluation will investigate the response to general implementation strategies at scale as well as more targeted strategies, akin to academic detailing, for selected sites which require additional focused resources.

**Trial registration:**

ClinicalTrials.gov registration #NCT07334795.

**Supplementary Information:**

The online version contains supplementary material available at 10.1186/s43058-026-00915-0.

Contributions to the literature
This study addresses a literature gap concerning implementation of antibiotic stewardship *at large scale* (~ 250 sites) and will provide key learnings about how integrated health systems can implement outpatient stewardship as a measurement-driven implementation program, leveraging a shared EHR, standardized dashboards, and routine feedback loops to support adoption *and* sustainment.It tests the established use of evidence-based implementation strategies (e.g., audit & feedback) at scale by investigating the use of phased intensification; specifically, employing an initial phase with minimal site-level focus followed by more intensive facilitation (termed “Boost”; i.e., academic detailing) for sites needing more specific support and will provide implementation science learnings about the potential benefit of enhanced support for stewardship programs: not only whether “Boost” improves outcomes, but which settings and contexts respond to intensification and what non-response implies for future strategy selection.It is among the largest U.S. efforts to improve pediatric outpatient antibiotic prescribing in ambulatory settings and will provide insights for stewardship programs that must balance focused efforts and efficiency at scale, avoiding a one-size-fits-all implementation but still maintaining an enterprise-wide implementation strategy.Findings will offer a transferable approach for embedding evaluation into routine operations, supporting the broader goal of generalizable scale-up methods for outpatient stewardship across large, dispersed health systems.Our experience will provide insights about what strategies can be standardized and what approaches might benefit from a more tailored approach when disseminating outpatient stewardship programs across multiple specialties and regions within a single Enterprise.

## Background

### Ambulatory antibiotic use, overuse, and misuse in children

Studies have demonstrated that antibiotics are overused – some estimate that up to one-third of antibiotics prescribed in the US in outpatient settings may be unnecessary [1–3]. In childhood, antibiotic use is nearly universal, and inappropriate prescribing is a well-recognized concern. In a sample of 759 children in the US with private medical insurance, Kissler and colleagues found that by 5 years of age, children had received a mean of 6.8 antibiotic courses and 91% had received at least one course [4]. Most antibiotics are prescribed in outpatient settings and respiratory conditions account for > 70% of these prescriptions for children [5]. For example, acute otitis media (AOM) is the single most common reason for antibiotics in children, resulting in an estimated 5 million affected children and 10 million antibiotic prescriptions annually in the United States (US) [1, 5, 6]. Even when an antibiotic is indicated, it may be misused if the *choice* of agent and *duration *deviate from evidence-based and professional society recommendations [7, 8]. Broad-spectrum antibiotics are frequently used in place of recommended narrow-spectrum options, and courses longer than the recommended duration are commonly prescribed [9–13].

These patterns of overuse and misuse have significant consequences. Unnecessary antibiotic exposure promotes the emergence of antibiotic-resistant organisms [14]. Antibiotics also carry direct risks for pediatric patients: they disrupt the normal microbiome and have been linked to increased risk of certain chronic conditions [15–18]. Emerging data also suggest the burden of antimicrobial exposure in early life can impair the immunologic response to immunization [19, 20] and diminish vaccine efficacy. Additionally, a notable proportion of children experience adverse drug events from antibiotics including diarrhea, rash, and rarely, severe allergic reactions or *Clostridioides difficile *infection [11, 21]. Reported rates of these adverse drug-related events may underestimate the actual frequency of these reactions and side effects since many may not be reported by a child's caregiver or result in contact with the medical system. In addition to these more apparent consequences of antibiotic overuse and misuse there are also direct (e.g. more healthcare visits due to side effects) and delayed indirect economic impacts (e.g. lost school and workdays) that have significant societal burden. Thus, reducing inappropriate antibiotic use in children is a public health imperative to improve the acute and long-term outcomes for pediatric patients as well as minimizing unnecessary costs for health systems and society.

To address these concerns and with increasing recognition of the need to promote judicious antibiotic use in ambulatory care, the US Centers for Disease Control and Prevention (CDC) released the Core Elements of Outpatient Antibiotic Stewardship in 2016 with an expected update to be released in 2026 emphasizing how health systems can contribute to ambulatory antibiotic stewardship [22]. This framework provides strategies to achieve improvements in ambulatory antibiotic prescribing based on four core elements: commitment, action for policy and practice, tracking and reporting, and education and expertise. A variety of interventions using elements from the CDC framework have been implemented and studied to decrease unnecessarily prescribed antibiotics [23–25] and to optimize antibiotic selection and duration when antibiotics are prescribed [26–28]. However, prescriptions that are unnecessary, overly broad-spectrum, and treatment courses longer than the recommended duration persist and are common [29–31].

Despite literature suggesting improvements in appropriate antibiotic prescribing (right drug, dose, and duration when antibiotics are truly needed) are achievable and yield better patient outcomes, effective and sustained implementation remains elusive. Shifting threats to adherence, including those internal to a system or environment as well as external factors (e.g. case mix changes) often undermine gains from previous implementations. Therefore, we aim to utilize the following strategies in combination to enact large-scale, sustainable implementation: 1) audit and feedback, 2) clinical decision support tools in the EMR to guide clinicians at the point of care to recommended narrow-spectrum antibiotics for the recommended duration, 3) clinician champions and local leaders to influence peers and sustain focus on stewardship goals, 4) educational outreach with updated and regularly renewed system guidelines and resources for each respiratory condition and peer stewardship partners to provide personalized training and problem-solving with clinicians to address knowledge gaps, concerns, and misconceptions, and 5) patient education and engagement via brochures, shared-decision making aids, or other approaches to help clarify caregiver expectations about antibiotics when appropriate, their role, and symptomatic management. Each of these strategies has shown promise in controlled or smaller-scale studies. The challenge remains how to integrate and scale all of these tactics in a unified ambulatory stewardship intervention across the varied care delivery environments of a geographically dispersed large health system that realizes and sustains improvements in antibiotic prescribing.

### Intermountain Health

Intermountain Health (IH) is a large, not-for-profit integrated health system in the Mountain West organized into three major geographic regions: Canyons (Central and Northern Utah, Idaho, and Western Wyoming), Peaks (Colorado, Eastern Wyoming, Montana, New Mexico), and Desert (Nevada, Arizona, & Southwest Utah). Each region includes urban, suburban, and rural communities (see Fig. 3 in Supplementary Information). This integrated structure with 33 hospitals and nearly 400 clinics has enabled IH to pursue ambitious system-wide quality improvement initiatives [32–36]. These attributes create a conducive environment for large-scale implementation of best practices, such as antibiotic stewardship, with support from leadership and alignment with system priorities. Prior and ongoing ambulatory antibiotic stewardship efforts in our system (see Table S2 and Fig. S4) demonstrated reductions in antibiotic prescribing for respiratory conditions in urgent care (UC) [23] and identified opportunities for improving prescription durations for common infectious conditions in primary care (PC) [29]. Other ongoing efforts seek to understand optimal strategies to increase the uptake of watchful waiting for pediatric ear infections [37, 38] and sustaining improvements in respiratory antibiotic prescribing in UC.

Despite these successes, prior outpatient stewardship activities at IH have been siloed – confined within particular service lines (UC or PC only, for example) or specific regions. A more coordinated and unified system-wide approach is needed to achieve substantial improvements in pediatric antibiotic prescribing, sustain them, and create a durable ambulatory antibiotic stewardship initiative in perpetuity that can adapt to external pressures as well as patient, provider, and pathogen changes along with evolving evidence.

In addition to its history of antibiotic stewardship, IH is well-positioned to undertake this project based on the following unique characteristics:A unified electronic health record (Epic) across all ambulatory and inpatient sitesAn established culture of best-practice implementation and continuous quality improvementSystem-wide infrastructure for implementing at scale including the Healthcare Delivery Institute, the Clinical Programs, and the Clinical Best Practice Integration (cBPI) model (see Fig. 1).

**Fig. 1 Fig1:**
[figure not shown]
The Clinical Best Practice Integration (cBPI) model [39]

Each of these factors will be leveraged for the current project. EMR tools will be implemented across the system and trainings on the use of these tools rolled out with each implementation. The Healthcare Delivery Institute will manage the project and Clinical Programs are already working in lock-step to implement evidence based practice [40] and will leverage this relationship to implement and scale evidence-based stewardship for this project. The cBPI model [39] provides a clear framework already in use across IH that leverages and simplifies relevant implementation and improvement science tools to maximize the success of the stewardship project.

In combination, these IH characteristics (size, integrated EMR, culture of implementation/improvement, Healthcare Delivery Institute, Clinical Programs, cBPI) position IH to successfully implement a novel, unifying, outpatient antibiotic stewardship initiative at unprecedented scale. Additionally, our size and diversity provide singular opportunities to examine how context influences implementation. Within the ~ 250 care sites that will participate in this project there is substantial heterogeneity – from small rural clinics to large urban academic practices, general family medicine clinics to pediatric offices and telehealth, and a range of patient demographic groups. This heterogeneity across a broad geographic area of the US will enhance the generalizability of lessons learned. The integration of these sites within one system provides a common infrastructure that can be leveraged to deploy a standardized intervention and comprehensively assess its impacts across Intermountain and within regions.

In summary, IH offers a unique combination of breadth and connectedness, enabling both large-scale change and rigorous, nuanced evaluation of the implemented intervention to effect that change at the system, region, and care setting levels. Herein, we describe our implementation aims and strategies to optimize antibiotic selection and prescription duration for acute respiratory tract infections in children.

## Methods and design

This project, named Stewardship in Community Outpatient settings – Resources and Engagement – Pediatrics (SCORE-Peds), leverages several key structures from Quality Improvement (QI) and Implementation Science (IS) in equal measure as described by Beidas et al. [41] The cBPI model is designed to leverage the strengths of QI and IS to integrate best practices across Intermountain. For example, the design and testing of digital technology solutions (e.g., EMR modifications) in the Measure & Report phase involves Plan-Do-Study-Act (PDSA) cycles to optimize the utility of these tools (Fig. 2). Likewise, sites will be selected for Boost using data on variation (QI). In response, QI teams will work at a local level to conduct site-specific root cause analyses and improvement cycles. In a complementary fashion the project employs specific implementation strategies from the Expert Recommendations for Implementing Change (ERIC) [42] established in IS studies of antibiotic stewardship. These include audit and feedback, clinician education, and facilitation (see Table 3 in supplementary information). We recognize that these approaches stem from separate traditions with differing approaches; however, like Beidas et al., we believe that a combined approach best serves the overall aims of this project as stated previously. Accordingly, we will reference both QI and IS approaches in the methods and design.

This initiative corresponds to the receipt of a Health Services Implementation Initiative (HSII) award [43] from the Patient-Centered Outcomes Research Institute (PCORI) in January of 2025. A foundation for this and similar initiatives was laid previously using a PCORI capacity building award under the HSII. Using capacity building funds, IH built a standardized dashboard system to use across all IH cBPI projects known as the cBPI Standardized Measurement and Reporting System (cSMART). In addition, specific to this project, the first two cBPI phases [39], Search/Develop/Identify and Define and Certify, were completed in preparation for the award. During the planning phase of SCORE-Peds, IH established workstreams to conduct key planning activities (see Fig. 2) corresponding to the measure and report phases of cBPI. During 2026 and 2027, IH will implement SCORE-Peds across all regions in all ambulatory settings where target conditions are treated. (Additional detail; see Table S3 for the Logic Model driving Quality Improvement [QI] and Table S4 for project activities).

**Fig. 2 Fig2:**
[figure not shown]
Phased implementation of SCORE-Peds

### Study aims and hypotheses

#### Aim 1: Evaluate the overall effectiveness of core implementation strategies at driving high adherence to antibiotic guidelines for ARTIs across a large number of diverse clinical settings

##### Rationale

The project spans ~ 250 sites across the intermountain west (see Fig. S3) and multiple care settings (pediatrics, family medicine, urgent care, ED, telehealth) and offers a unique opportunity to evaluate the effectiveness of previously tested implementation strategies at scale.

##### Key questions

Was adherence to antibiotic guidelines for ARTIs achieved (see Table 1 and Primary Innovation)?Did contextual factors (e.g., rural vs. urban, practice type, clinician role) influence adherence rates?Exploratory question: How did adherence change *over time* and did the time course differ by context?

##### Hypothesis

High adherence in each region will be achieved following implementation.

#### Aim 2: Identify how adherence varies by context and examine use of implementation strategies and contextual determinants

##### Rationale

The wide variety of geography and clinic types allows us to examine how contextual factors influence adherence, as well as use of implementation strategies while holding some things constant (e.g., shared EMR, corporate structure).

##### Key questions

How do contextual factors (e.g., rural vs. urban, practice type, clinician role) influence adherence rates? How did that emerge over time and was the time course different in different contexts?What organizational, regional, and site-level factors facilitate or impede scale-up?Which implementation strategies are deemed most effective at driving high adherence based on contextual factors?Setting is key: traditionally, antibiotic stewardship has been siloed into specialties (e.g., pediatrics, family medicine, urgent care, ED). How does a large cross-setting initiative work?

##### Hypothesis

Use of implementation strategies (i.e., engagement) will correlate with changes in adherence.

#### Aim 3: Assess the impact of Boost on effectiveness and implementation outcomes

##### Rationale

The project includes an exploratory aim to test “Boost” – a more intensive implementation support program akin to academic detailing with sites that are less responsive to initial general implementation and therefore have lower rates of adoption. This allows for comparison of foundational vs. enhanced strategies and focused resource utilization.

##### Key questions

Do academic detailing and similarly intensified strategies improve adoption?How do champions, clinical peer stewardship partners and site facilitators influence implementation climate and sustainment?

##### Hypothesis

Sites with lower adoption rates who receive the Boost will demonstrate increased use of implementation strategies and increased adherence compared to sites that did not receive Boost.

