### Study procedures

This evaluation will use observational and quasi-experimental designs to examine effectiveness and implementation outcomes as outlined below. The implementation will proceed in two waves with approximately half of the sites in each wave. To maximize efficiency and likelihood of adoption, sites will be assigned to waves based on region rather than by randomization (see Fig. 2). The first wave includes all sites in the Canyons region with Peaks and Desert regions in the second wave. Each wave will provide a pre-post design using archival baseline data. In addition, the Peaks and Desert regions serve as a comparison group for the Canyons implementation to compensate for possible secular trends. We plan to examine adherence rates overall (aim 1), across sites (aim 2), and as a function of response to Boost (aim 3).

In addition, we plan to examine the use of implementation strategies overall (aim 1), across sites (aim 2), and in response to Boost (aim 3). This examination is based on several key indicators including: the number and frequency of trainings, attendance at trainings, and the frequency with which providers and sites access tools such as EMR utilities (e.g., preference lists, order sets, smart sets), c-SMART dashboards, and audit & feedback reports. We expect that the use of these strategies will vary by site and correlate with changes in adherence.

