### Other outcomes

Treatment failure will be examined as a balancing measure and defined as a return visit between 2 and 14 days for the same ARTI diagnosis where a new antibiotic prescription was given.

In terms of implementation, the study will evaluate the proportion of sites using clinical decision support tools (e.g., preference lists for antibiotic selection and duration), the percentage of clinicians engaging with audit-and-feedback dashboards, and indicators of implementation engagement such as attendance at trainings, and participation in site facilitation.

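### Some of the Aim 3 indicators of strategy use overlap with what Boost itself supplies, so on those items a Boost versus non-Boost difference is wholly or partly built in

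*Protocol article*

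**What the plan says.** Aim 3 has a two-part hypothesis: Boost sites "will demonstrate increased use of implementation strategies and increased adherence compared to sites that did not receive Boost".

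Study procedures says that "we plan to examine the use of implementation strategies overall (aim 1), across sites (aim 2), and in response to Boost (aim 3"), and gives the indicators on which this rests: "the number and frequency of trainings, attendance at trainings, and the frequency with which providers and sites access tools such as EMR utilities", together with "c-SMART dashboards, and audit & feedback reports".

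Other outcomes adds, for the study as a whole, "the proportion of sites using clinical decision support tools", "the percentage of clinicians engaging with audit-and-feedback dashboards", and "indicators of implementation engagement such as attendance at trainings, and participation in site facilitation".

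The contributions box after the abstract describes the phased design as "employing an initial phase with minimal site-level focus followed by more intensive facilitation", and names the second phase Boost. The Aim 3 rationale likens Boost to academic detailing. The Aim 3 key questions name champions, peer stewardship partners and site facilitators. The Background lists personalised training by peer partners among the general strategies.

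The article does not say that activity delivered under Boost is left out of the strategy-use indicators when Boost and non-Boost sites are compared.

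**The concern.** An outcome meant to show the response to an intervention should not contain the intervention. If Boost is extra facilitation and one indicator of strategy use is taking part in facilitation, Boost sites score higher on that indicator because they were chosen for Boost. A count of trainings held has the same weakness wherever Boost contacts are logged as trainings, since it measures supply and not uptake.

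What is at stake is how Aim 3 is read. The Discussion says that a failure of low-adoption sites to improve under Boost would itself be informative, because it would suggest that intensifying these strategies is not the answer. That inference depends on knowing whether clinicians took up the strategies. If the reported rise in use comes from delivered sessions, a finding that use rose while adherence did not cannot separate two explanations: clinicians engaged and it did not help, or they never engaged beyond the sessions brought to them.

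**Working it through.** The article gives no figure on this point. Its only numerical design claim, power above 99%, concerns adherence and plays no part here. The check is to classify each listed indicator by whether delivering Boost moves it directly.

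| Indicator | Where listed | Relation to Boost delivery |
|---|---|---|
| Participation in site facilitation | Other outcomes | Direct overlap: Boost is described as more intensive facilitation |
| Number and frequency of trainings | Study procedures | Supply count; overlaps if Boost sessions are logged as trainings |
| Attendance at trainings | Both | Possible partial overlap: more sessions give more chances to attend, but clinicians must turn up |
| Access to EMR utilities | Study procedures | Not produced by delivery |
| Access to c-SMART dashboards | Study procedures | Not produced by delivery |
| Access to audit and feedback reports | Study procedures | Not produced by delivery |
| Sites using decision support tools | Other outcomes | Not produced by delivery |
| Clinicians engaging with feedback dashboards | Other outcomes | Not produced by delivery |

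The tally is 2 that overlap or plausibly do, 1 possible, and 5 that do not: 2 + 1 + 5 = 8.

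For a count-type indicator, let *m*B and *m*N be the mean activity per site that Boost and non-Boost sites would show without counting Boost contacts, and let *k* be the mean number of Boost-delivered contacts counted per Boost site. Then

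observed difference = (*m*B − *m*N) + *k*.

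With no response to Boost and equal starting levels, *m*B = *m*N and the observed difference equals *k*, which is positive by assignment.

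The article gives none of *m*B, *m*N or *k*, so the following values are assumptions chosen only to show the mechanism. Boost sites are selected for low adoption, so suppose their own activity is 25% lower.

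- *m*N = 4, *k* = 2: *m*B = 0.75 × 4 = 3; counted total 3 + 2 = 5 against 4. Boost sites appear 25% higher (5/4 = 1.25) while their own activity is 25% lower.
- *m*N = 8, *k* = 2: *m*B = 0.75 × 8 = 6; counted total 6 + 2 = 8 against 8. The real deficit is hidden.
- *m*N = 8, *k* = 4: counted total 6 + 4 = 10 against 8. Boost sites again appear 25% higher (10/8 = 1.25).
- *k* = 0 (Boost sessions not logged as trainings): the training count carries no built-in difference. The facilitation item still does.

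The direction of the problem follows from the definitions. Its size depends wholly on *k*.

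**The case against.** A reader might infer that the strategy-use half of the hypothesis is met simply by delivering Boost, even if no clinician changes behaviour. The documents do not support that. Five of the eight indicators need clinicians or sites to act. The article states no composite and no decision rule, so nothing lets the delivery items decide the hypothesis alone. Any false-positive percentage would come from assumed inputs and describe a rule the article does not contain.

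Other points on that side also have weight:

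- The article does not list the contents of Boost. That Boost sessions would be logged as trainings is an inference from the likeness to academic detailing and from the peer partners named under Aim 3. The Intermountain Health section describes trainings as rolled out with each implementation, so they are also a system-wide strategy.
- Facilitation appears under Other outcomes and not in the Study procedures list that is tied explicitly to Aim 3.
- Tool access is recorded separately, so a careful analyst could see whether clinicians engaged.
- The Aim 3 rationale labels the aim exploratory, the Aim 3 analysis described under Data collection and analysis compares adherence only, and Challenges and limitations disclaims a rigorous test of implementation hypotheses.

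These points limit the concern without removing it. How indicators are combined can be left to an analysis plan. The overlap itself, however, lies in what the article does state: Study procedures places a supply count among the indicators to be examined in response to Boost, and Other outcomes calls taking part in facilitation a sign of engagement. An exploratory label does not make an outcome separate from its exposure.

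**Conclusion.** The point holds in a limited form. On participation in site facilitation, and on the number and frequency of trainings to the extent that Boost contacts are logged there, a difference between Boost and non-Boost sites is wholly or partly built in and cannot show a response to Boost. Attendance may be affected in part.

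The tool-access and decision-support indicators, the adoption outcome (derived from prescribing) and the adherence half of the Aim 3 hypothesis are not affected.

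The size cannot be stated from the article, and the worked values above are illustrative only. The conclusion rests on two readings: that facilitation under Boost counts as site facilitation, which the description of Boost supports directly, and that some Boost contacts would count as trainings, which is plausible but not stated. The consequence is a risk of misreading a secondary part of an exploratory aim, and it is inexpensive to remove.

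**What to change.** For the Aim 3 comparison:

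1. Report trainings, detailing and facilitation delivered as part of Boost separately, as Boost dose or fidelity, and do not count them as use of implementation strategies.
2. Rest the strategy-use half of the hypothesis on indicators already listed and open to every site: EMR utility and decision-support use, c-SMART dashboard access, and audit and feedback report access.
3. Express these per prescriber or per eligible encounter, so that sites of different size can be compared.

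The cost is a change of wording and a flag on Boost-delivered sessions so that they can be separated. The reported increase in strategy use will be smaller. The indicators in step 2 are already named in the article, so no new outcome is needed.
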